# Efficacy and safety of rapid intermittent correction compared with slow continuous correction with hypertonic saline in patients with moderately severe or severe symptomatic hyponatremia: study protocol for a randomized controlled trial (SALSA trial)

**DOI:** 10.1186/s13063-017-1865-z

**Published:** 2017-03-29

**Keywords:** Hyponatremia, Hypertonic saline, Treatment, Osmotic demyelination syndrome

## Abstract

**Background:**

Hyponatremia is the most common electrolyte imbalance encountered in clinical practice, associated with increased mortality and length of hospital stay. However, no high-quality evidence regarding whether hypertonic saline is best administered as a continuous infusion or a bolus injection has been found to date. Therefore, in the current study, we will evaluate the efficacy and safety of rapid intermittent correction compared with slow continuous correction with hypertonic saline in patients with moderately severe or severe symptomatic hyponatremia.

**Methods/design:**

This is a prospective, investigator-initiated, multicenter, open-label, randomized controlled study with two experimental therapy groups. A total of 178 patients with severe symptomatic hyponatremia will be enrolled and randomly assigned to receive either rapid intermittent bolus or slow continuous infusion management with hypertonic saline. The primary outcome is the incidence of overcorrection at any given period over 2 days. The secondary outcomes will include the efficacy and safety of two other approaches to the treatment of hyponatremia with 3% hypertonic saline.

**Discussion:**

This is the first clinical trial to investigate the efficacy and safety of rapid intermittent correction compared with slow continuous correction with hypertonic saline in patients with moderately severe or severe hyponatremia.

**Trial registration:**

ClinicalTrials.gov, identifier number: NCT02887469. Registered on 1 August 2016.

**Electronic supplementary material:**

The online version of this article (doi:10.1186/s13063-017-1865-z) contains supplementary material, which is available to authorized users.

## Background

Hyponatremia is the most common electrolyte imbalance encountered in clinical practice, and is associated with increased mortality and length of hospital stay [1]. The symptoms related to hyponatremia span a broad range from moderately severe (cognitive test abnormalities, gait impairment) to severe or life-threatening (hypoxemia, coma, and epilepsy) [2–5]. Treatment strategies for hyponatremia differ according to the severity of clinical symptoms and duration of hyponatremia [6]. The extent and rate of increase in serum sodium (sNa) levels during treatment are crucial. Overcorrection of chronic hyponatremia may result in osmotic demyelination syndrome (ODS), whereas undercorrection may be insufficient to prevent its life-threatening manifestations [6–9].

Several methods for continuous infusion of hypertonic saline have been used to guide the rate of fluid administration to achieve the required sNa target [10, 11]. The increase in sNa should be limited to 8–10 mmol/L within the first 24 h and 18 mmol/L within 48 h [11, 12]. As these methods were based on static models of a dynamic clinical situation, they had a bias toward overcorrection of hyponatremia [1, 13–15].

Recent guidelines have recommended prompt infusion of 100–150 mL of 3% saline over 10–20 min to increase the sNa by 4–6 mmol/L during the first hour. A pragmatic approach to treatment with hypertonic fluid is to use small, fixed boluses to achieve controlled incremental increases in sNa [1, 13–17]. However, this recommendation was the result of small randomized trials [18], case reports with small numbers of patients [14, 19], and expert opinion [20–23]. No high-quality evidence has been reported regarding whether hypertonic saline is best administered as a continuous infusion (preferred by most) or as a rapid intermittent bolus injection. The purpose of the present study was to investigate the efficacy and safety of rapid intermittent correction compared with slow continuous correction with hypertonic saline in patients with symptomatic severe hyponatremia. Furthermore, the study will examine prevailing conceptions regarding the optimal treatment of severe symptomatic hyponatremia.

## Methods/design

### Hypothesis

The use of intermittent bolus therapy with 3% sodium chloride will prevent and/or ameliorate ODS in patients with hyponatremia treated with hypertonic saline. Compared to the use of standard slow continuous infusion with 3% hypertonic saline, the incidence of overcorrection will be lower in patients with moderately severe or severe hyponatremia.

### Study design

This study is a prospective, investigator-initiated, multicenter, open-label, randomized controlled study with two experimental therapy groups. We have followed the Standard Protocol Items: Recommendations for Interventional Trials (SPIRIT) 2013 Statement which defines standard protocol items for clinical trials [24] (see Additional file 1). The study algorithm is depicted in Fig. 1 and the SPIRIT and study schedule are given in Figs. 2 and 3. After enrollment, clinical follow-up will be performed 2 days after treatment with 3% hypertonic saline.

**Fig. 1 Fig1:**
[figure not shown]
Study algorithm. *ER* emergency room

**Fig. 2 Fig2:**
[figure not shown]
Schedule of enrollment, interventions, and assessments according to the Standard Protocol Items: Recommendations for Interventional Trials (SPIRIT) guideline. *GCS* Glasgow Coma Scale

**Fig. 3 Fig3:**
[figure not shown]
Study schedule. *R* randomization, *ER* emergency room, *CBC* complete blood count, *Glu* glucose, *AST* aspartate aminotransferase, *ALT* alanine aminotransferase, *Chol* cholesterol, *BUN* blood urea nitrogen, *Cr* creatinine, *tCO*
*2* total CO2, *TFT* thyroid function test, *ACTH* rapid adrenocorticotropic hormone, *Osm* Osmolality, *U/A* urinalysis, *E'* electrolyte, *UOsm* Urine osmolality, *GCS* Glasgow Coma Scale

### Study participants and measurements

All participants will be selected from among patients visiting the emergency rooms of two general hospitals in Korea (Seoul National University Bundang Hospital, Seoul National University Boramae Medical Center). Patients aged over 18 years who have moderately severe to severe symptoms and glucose-corrected sNa [25] ≤125 mmol/L on the first blood test will be screened for study participation. Moderate symptoms include nausea, headache, drowsiness, general weakness, and malaise [1, 26, 27]. Severe symptoms include vomiting, stupor, seizure, and coma (Glasgow Coma Scale (GCS)).

The following assessments will be performed during the initial emergency room encounter: (1) completion of questionnaire on medical and drug history including the use of antihypertensive medication, diuretics, nonsteroidal anti-inflammatory drugs, selective serotonin reuptake inhibitors, antiepileptic drugs, steroids, and synthyroid, (2) physical examination of all body systems, (3) measurement of height and weight, (4) blood pressure and pulse rate measurement, and (5) assessment of psychological status. Participants, who meet all of the inclusion criteria, do not require exclusion on the basis of the exclusion criteria, and provide written informed consent will be eligible for this study (Table 1).

**Table 1 Tab1:** Inclusion and exclusion criteria

Inclusion criteria	Exclusion criteria
18 years and older	Pseudo-hyponatremia (serum osmolality >275 mOsm/kg)
	Primary polydipsia (urine osmolality ≤100 mOsm/kg)
	Glucose-corrected serum sodium >125 mmol/L
	Initial arterial hypotension (SBP <90 mmHg and MAP <70 mmHg)
Glucose-corrected serum sodium ≤125 mmol/L	Anuria or urinary outlet obstruction
	Decompensated LC (LC with ascites or diuretics use or history of hepatic encephalopathy and varices)
	Bilirubin >2 mg/dL, transaminase levels >2.5 times the upper limit of normal)
Symptomatic patients	Uncontrolled diabetes mellitus (HbA1C >9%)
Moderately severe:	Women who are pregnant or breastfeeding
nausea without vomiting, drowsiness, headache, general weakness, malaise	Within the 3 months prior to randomization, history of cardiac surgery excluding PCA, acute myocardial infarction, sustained ventricular tachycardia, ventricular fibrillation, acute coronary syndrome, cerebrovascular trauma, and increased intracranial pressure
Severe:	
vomiting, stupor, seizures, coma (GCS ≤8)	

*GCS* Glasgow Coma Scale, *SBP* systolic blood pressure, *MAP* mean arterial pressure, *LC* liver cirrhosis, *HbA1C* glycosylated hemoglobin, *PCA* percutaneous coronary angioplasty

Serum creatinine (SCr) will be measured using the isotope dilution mass spectrometry-traceable method with a Toshiba TBA 200FR Analyzer (Toshiba, Tokyo, Japan). The estimated glomerular filtration rate (eGFR) will be calculated using the Chronic Kidney Disease Epidemiology Collaboration (CKD EPI) equation [28].

### Randomization

A research coordinator will perform the randomization. A list of random numbers will be generated by an independent statistician. Eligible participants will be randomly assigned 1:1 to either the slow continuous correction group or the rapid intermittent correction group in accordance with the predefined randomization list with a block size of 2. Randomization will be stratified based on the symptom severity related to hyponatremia (moderately severe or severe).

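### A fixed block size of 2 in an open-label trial, published during recruitment, lets anyone who knows a stratum's earlier assignments deduce up to half of all allocations

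*Protocol article*

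**What the plan says.** The Randomization section of the protocol article sets the whole scheme. "A list of random numbers will be generated by an independent statistician", and then "A research coordinator will perform the randomization". The ratio is 1:1, "in accordance with the predefined randomization list with a block size of 2". The only stratification factor named is symptom severity: "Randomization will be stratified based on the symptom severity related to hyponatremia (moderately severe or severe").

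Study design describes the trial as a "prospective, investigator-initiated, multicenter, open-label, randomized controlled study with two experimental therapy groups", so each assignment is visible once treatment starts. Study participants and measurements says that recruitment is from "patients visiting the emergency rooms of two general hospitals in Korea". The article does not say whether each hospital has its own list or both draw from one list per stratum.

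The article is dated 29 March 2017. Trial status gives recruitment from August 2016 to an expected end in July 2018, so the block size became public with more than a year of planned recruitment left.

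**The concern.** A block of 2 with 1:1 allocation has only two possible orders. Once the first patient of a pair is seen to receive a bolus or an infusion, the arm of the next patient in that stratum follows. Having an independent statistician make the list does not prevent this, and neither does concealed release of each assignment: the second assignment is deduced from the first, not read from the list.

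The danger is selection. Someone who knows or suspects the next arm can decide whether, or when, to enter a particular patient. Table 1 leaves room for that decision, because general weakness and malaise qualify as moderately severe symptoms and the Discussion itself calls them usually nonspecific. If patients thought more likely to overcorrect are entered preferentially when one arm is due, the arms differ in baseline risk of the primary outcome. A laboratory-measured outcome does not protect against this, because the bias lies in who enters each arm and not in how the outcome is read.

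**Working it through.** **The plan's own figure.** The article gives no figure for predictability. It does give 89 per group, from 20% against 5%, two-sided 5% significance, 80% power and 15% dropout (Sample size calculation). With a pooled chi-square formula:

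n = [1.960·√(2·0.125·0.875) + 0.842·√(0.20·0.80 + 0.05·0.95)]² / 0.15² = (0.917 + 0.383)² / 0.0225 ≈ 75.1

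This is 76 evaluable per group. Dividing 75.1 by 0.85 gives 88.4, or 89 when rounded up. The stated figure reproduces and is not affected by this point. The calculations below use 152 evaluable patients (2 × 76) and a common event risk of 12.5%, the mean of 5% and 20%.

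**Predictability with full knowledge of the stratum.** For a fixed block of 2m, the share of assignments that are certain from earlier ones is 1/(m+1). The best-guess rate is g = [m + (4^m / C(2m,m) − 1)/2] / (2m). Exact enumeration of all blocks agrees.

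| Block size | Certain | Best-guess rate g |
|---|---|---|
| 2 | 50% | 75.0% |
| 4 | 33.3% | 70.8% |
| 6 | 25% | 68.3% |

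For blocks of 2, 50% of 178 is 89 assignments. An undisclosed random mix of 4 and 6 still allows about 69% correct guesses (simulation) to someone who tracks the running imbalance, but block ends can seldom be identified with certainty.

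**Predictability with a shared list and own-site knowledge only.** Assume that patients come from the two sites in equal numbers. A site's last patient was first in a pair with probability 1/2, and the next patient in that stratum comes from the same site with probability 1/2. The two therefore share a pair with probability 1/4. Guessing the opposite of the last own-site assignment is right with probability 1/4 + 3/4 × 1/2 = 62.5%. Simulation gives about 62%.

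**Effect on the false-positive risk.** Assume no treatment effect. Suppose that a patient's risk is shifted by +δ when one arm is guessed and by −δ when the other is, and that this is done for every guess. The expected difference between arms is then 2δ(2g − 1). The standard error is √(2 × 0.125 × 0.875 / 76) = 0.0536.

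- Block 2, δ = 5 points: difference 10 × 0.5 = 5.0 points, or 0.932 standard errors. P(Z > 1.028) + P(Z < −2.892) = 15.4%. Simulations gave 15–16%.
- Block 2, δ = 2.5 points: difference 2.5 points, 7.5%. Simulations gave 7.4–7.6%.
- Known fixed block of 4, acting only on certain assignments (one third of patients): differences 3.33 and 1.67 points, 9.5% and 6.1%.
- Known fixed block of 4, acting on every best guess: 10 × 0.417 = 4.17 and 5 × 0.417 = 2.08 points, 12.1% and 6.7%.
- Block 2, shared list, own-site knowledge, δ = 5 points: 10 × 0.25 = 2.5 points, 7.5%. Simulation gave 7.4%.
- Block 2, only half of the known allocations steered, δ = 5 points: difference 2.5 points, 7.5%. Simulation gave 7.8%.
- No steering: about 5%.

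**First patient of each pair.** That assignment is a fair draw whatever went before. With every second patient steered by 5 points, the test restricted to first-in-pair patients kept a false-positive rate of about 5% (5.1% in 6,000 simulated trials; 5.3% in a repeat).

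**The case against.** The strongest objection is that predictability is conditional. A reader might infer that recruiters know every second assignment and that concealment fails for half of all patients. The article does not support that as fact. Certainty requires knowing all earlier assignments in the stratum, there are two hospitals, and the article is silent on whether they share a list. With a shared list and own-site knowledge the hit rate is about 62%. This qualification stands. It does not remove the weakness: anyone who sees both sites' assignments would still be certain, and separate lists per site would restore certainty at each site.

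Second, the 16% needs every deducible allocation to be steered, by someone able to pick patients whose overcorrection risk differs by 10 points (7.5% against 17.5%). The documents contain no such figure. This also stands. So does the point that a fair comparison lets a recruiter facing blocks of 4 act on good guesses, which narrows the contrast from 16% against 9% to 16% against 12%.

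Third, a reader might think that the bias cannot be handled in the analysis. That is wrong, because the first-in-pair comparison is free of it, at the price of half the sample.

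Fourth, the routes for steering are limited. Entry also needs a glucose-corrected sodium of 125 mmol/L or below. Malaise and general weakness both belong to the moderately severe stratum, so they leave room over entry and timing more than over stratum.

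Finally, the article does not say that the coordinator can see the list. How assignments are released is detail for the full protocol, and no criticism is made of it here.

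**Conclusion.** The point holds as a design weakness. The combination of a fixed block of 2, unmasked treatment and publication during recruitment makes up to 50% of allocations deducible for anyone who knows the stratum's history, and gives a lesser advantage (about 62% correct, assuming an equal site split) to a recruiter who knows only one site of a shared list.

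On assumed steering with no treatment effect, false-positive risk is about 7–8% for ±2.5 points and about 16% for ±5 points, the latter a worst case. Known fixed blocks of 4 would give about 6–7% and 9–12%. These figures rest on the assumed shifts, 152 evaluable patients and a 12.5% risk. They show what the scheme permits and do not estimate what happened: the article gives no evidence that enrolment was steered.

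**What to change.** **Remaining patients.** Replace the list with permuted blocks of randomly varying size (for example 4 and 6) within each severity stratum. Withhold the sizes from recruiting staff and from public documents until recruitment ends. Release each assignment only after eligibility and stratum are recorded. State whether the list is shared or separate by site.

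**Patients already randomized in pairs.** Add a sensitivity analysis of the primary outcome restricted to the first patient of each pair, identified from the randomization list, and compare baseline characteristics by block position and arm. Report the scheme as used.

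**Cost.** This needs one new list from the independent statistician and a short amendment; the sample size does not change. Possible imbalance at the end of a stratum rises from 1 to at most 3. If every patient had been randomized in pairs, the sensitivity analysis would use half the sample, so its standard error would be about √2 ≈ 1.4 times larger, and it can support the main result but not replace it. The change reduces predictability without abolishing it: best guesses fall from 75% to about 69%, and the main gain is that assignments can seldom be known with certainty.

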### Physician’s practical treatment guidelines according to the sNa level

The principal purpose of this study will be to compare the rapid intermittent correction group to the slow continuous correction group [29]. According to a review of the medical literature on the treatment of hyponatremia, treatment with hypertonic (3%) saline is recommended in cases of severe symptomatic hyponatremia [1, 15, 16]. Therefore, the rate of infusion of 3% saline will be stratified based on the symptom severity in each group. After randomization, the participants will undergo either rapid intermittent correction or slow continuous correction of hyponatremia for 48 h. Treatment in the intermittent bolus group will comply with European guidelines published in 2014, and the slow continuous infusion will be guided by widely accepted methods [1, 13–16]. The treatment goals are to raise the sNa level by 5–9 mmol/L from the initial sNa and to achieve symptom relief within the first 24 h, and to raise the sNa level by 10–17 mmol/L from the initial sNa or ≤130 mmol/L, and to achieve symptom relief during the 48 h [10–12]. We will also check for overcorrection at every sample time point and conduct relowering treatment. Relowering treatment is performed as below if the achieved sNa level is ≥10 mmol/L at any sample time point within the first 24 h or the achieved sNa level is ≥18 mmol/L at any sample time point within 48 h [1, 13–16]. The treatment goal, relowering treatment strategy, and cause-specific treatment of hyponatremia will be applied to each group equally.

## Rapid intermittent bolus group (Fig. 4a)

### First 24 hours

In the case of moderately severe symptoms, the use of intravenous infusion of 2 mL/kg 3% hypertonic saline over 20 min (100 mL, 3% saline for unknown body weight) is recommended. In cases of severe symptoms, it is recommended to perform intravenous infusion of 4 mL/kg 3% hypertonic saline over 40 min (200 mL, 3% saline for unknown body weight). After the initial treatment, repeated infusion of 2 mL/kg 3% hypertonic saline over 20 min at every sample time point (at 1, 6, 12, 18, and 24 h) until the observation of a sNa level increase of 5–9 mmol/L from the initial sNa and symptom relief is recommended.

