### From 24 to 48 hours

In both moderately severe and severe cases of hyponatremia, repeated infusion of 2 mL/kg 3% hypertonic saline over 20 min at every sample time point (at 30, 36, 42, and 48 h) is recommended until the sNa level increases to 10–17 mmol/L from the initial sNa or until the sNa reaches 130 mmol/L, and until the symptoms improve.

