## Slow continuous correction group (Fig. 4b)

### First 24 hours

In the case of moderately severe symptoms, it is recommended to infuse 3% hypertonic saline at a rate of 0.5 mL/kg/h (25 mL/h, 3% saline for unknown body weight). In cases of severe symptoms, it is recommended to begin an infusion of 3% hypertonic saline at a rate of 1 mL/kg/h (50 mL/h, 3% saline for unknown body weight). After the initial treatment, the infusion protocol will be modified as below according to the sNa level at every sample time point (at 1, 6, 12, 18, and 24 h). If the sNa level increases to 5–9 mmol/L above the initial sNa level, accompanied by symptom relief, the 3% saline infusion should be discontinued regardless of changes in the sNa level. If the sNa level increases at a rate of under 0.5 mmol/h or 3 mmol/6 h, it is recommended to add 3% hypertonic saline infusion at a rate of 0.25 mL/kg/h to the previous infusion rate or to restart the infusion at 0.5 mL/kg/h if it was previously discontinued. If the sNa level demonstrates increases of over 0.5 mmol/h or 3 mmol/6 h, the rate of 3% hypertonic saline infusion should be maintained.

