### Safety issues

All adverse events related to overcorrection will be recorded and followed up during the study period or until resolution during treatment with 3% hypertonic saline. Any serious adverse events will be reported to investigators and the Ethics Committee. We will check for overcorrection at every sample time point and conduct relowering treatment as needed. Relowering treatment is performed as follows if the achieved sNa level is ≥10 mmol/L at any sample time point within the first 24 h or if the achieved sNa level is ≥18 mmol/L at any sample time point within 48 h: discontinuing ongoing active treatment; initiating infusion of 10 mL/kg of 5% dextrose over 1 h; and/or adding desmopressin 2 mcg [1].

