In the development of this protocol, we complied with recent guidelines, particularly in determining the target sNa levels, in the method of infusion of 3% hypertonic saline for the rapid correction group, and in the classification of symptoms of hyponatremia [1, 15, 16]. Recently published guidelines recommended prompt intravenous infusion of 100–150 mL 3% hypertonic saline over 10–20 min, repeated once or twice as needed, in the initial treatment of severe hyponatremia [1, 15, 16]. We adopted a weight-based approach (2 mL/kg) rather than the fixed 100–150-mL infusion volumes of 3% hypertonic saline in this study because Koreans tend to have smaller physiques than Westerners. Recent guidelines recommended discontinuing the infusion of hypertonic saline in cases of improvement of symptoms after a 5-mmol/L increase in sNa and initiating a diagnosis-specific treatment [1]. Our planned approach to decreases or no change in sNa levels during the diagnosis of hyponatremia and the initiation of cause specific treatment was to repeat a bolus infusion every 6 h until sNa incrementally increases to the target level and symptom relief were observed. This approach is different from the protocols recommended by recent guidelines [1]. In the slow continuous correction group, we adopted a 3% hypertonic saline infusion rate of 0.5–1 mL/kg/h, a widely known treatment approach [10, 11], according to symptom severity. Recent guidelines define indicative symptoms of cerebral edema as severe or moderate symptoms that can be attributed to hyponatremia [1]. In our study, general weakness and malaise, usually considered nonspecific, were included as moderate symptoms of hyponatremia. Our rationale for including these as symptoms of hyponatremia are as follows: first, patients start complaining of nausea and malaise as sNa concentration falls acutely below 125 mmol/L [27]. Malaise is thus a result of hyponatremia and is as significant as nausea. Second, patients with symptomatic hyponatremia, including weakness and malaise, should be treated with hypertonic saline [26]. As this clinical trial aims to compare the efficacy and safety of rapid versus slow hypertonic saline administration in the correction of hyponatremia, we included general weakness and malaise as hyponatremia-defining symptoms.

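### At the top of the sodium goal with symptoms persisting, the stop rules in both arms direct more saline, which is expected to pass the plan's own goal and, from +9 or +17 mmol/L, reach its relowering trigger

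*Protocol article*

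**What the plan says.** All references are to the protocol article.

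- **Goal, day 1** (Physician's practical treatment guidelines): "raise the sNa level by 5–9 mmol/L from the initial sNa and to achieve symptom relief within the first 24 h". For 48 h the goal is a rise of 10–17 mmol/L or a sodium of at most 130 mmol/L, again with symptom relief.
- **Bolus arm, First 24 hours:** "repeated infusion of 2 mL/kg 3% hypertonic saline over 20 min at every sample time point (at 1, 6, 12, 18, and 24 h"), to continue "until the observation of a sNa level increase of 5–9 mmol/L from the initial sNa and symptom relief is recommended".
- **Bolus arm, From 24 to 48 hours:** the same bolus at 30, 36, 42 and 48 h, "until the sNa level increases to 10–17 mmol/L from the initial sNa or until the sNa reaches 130 mmol/L, and until the symptoms improve".
- **Slow arm, First 24 hours:** "If the sNa level increases to 5–9 mmol/L above the initial sNa level, accompanied by symptom relief, the 3% saline infusion should be discontinued". Otherwise the rate is increased if sodium rose by less than 3 mmol per 6 h and maintained if it rose by more. The day 2 section has the same structure, with 10–17 mmol/L or 130 and a cut-off of 1.5 mmol per 6 h.
- **Relowering** (Safety issues, and also the treatment guidelines section): active treatment is discontinued and relowering begins "if the achieved sNa level is ≥10 mmol/L at any sample time point within the first 24 h", or at ≥18 within 48 h. I read these figures as rises from the initial value.
- **Primary outcome** (Outcome measures): a rise of more than 12 mmol/L within 24 h or more than 18 within 48 h. Relowering, and staying below 10 and 18 mmol/L, are secondary outcomes.

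**The concern.** The goal has an upper end (9 mmol/L on day 1; 17 mmol/L, or 130, on day 2), but that upper end does not stop saline. It does so only if symptoms have also been relieved. The first limit that acts on sodium alone is the relowering trigger, 1 mmol/L above the top of the goal. A patient just inside the goal with persisting symptoms is thus given a raising dose and may then qualify for a lowering one.

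The state is plausible, because the Discussion reports that "general weakness and malaise, usually considered nonspecific, were included as moderate symptoms of hyponatremia". Such complaints need not clear as sodium rises.

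What is at stake is patient safety and the meaning of the endpoints. Some relowering episodes, failures of target correction and primary events could follow from how the stop rule is worded.

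**Working it through.** **1. Trace the rule for a patient at the top of the goal with persisting symptoms.**

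- Bolus arm, +9 at 6, 12 or 18 h: the joint condition is not met, so another 2 mL/kg is recommended. The trigger (≥10) is not met, so nothing overrides this.
- Slow arm, +9 at the same times: the discontinuation clause does not apply. The rate rules then maintain or increase the infusion; none lowers it.
- Day 2, +17 at 30, 36 or 42 h: the same in both arms, because the trigger is ≥18.
- Day 2, sodium at 130 mmol/L: the same, although the stated goal is at most 130.

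**2. Size of the step.** The plan gives no figure for the effect of one of its own doses, so I use mass balance.

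Assumptions not in the document: 3% saline = 30 g/L = 513 mmol/L; total body water W = 0.5–0.6 L/kg; no net water gain or loss. Current sodium s is taken as 129 mmol/L for illustration.

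Rise = V × (513 − s) / (W + V), with V in L/kg.

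- One bolus, V = 0.002: 0.002 × 384 / 0.502 = 1.53; 0.002 × 384 / 0.602 = 1.28.
- Slow arm, 6 h at 0.5 mL/kg/h, V = 0.003: 1.152 / 0.503 = 2.29; 1.152 / 0.603 = 1.91.
- Slow arm, 6 h at 1 mL/kg/h (the starting rate for severe symptoms), V = 0.006: 2.304 / 0.506 = 4.55; 2.304 / 0.606 = 3.80.

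| Start | Further saline | Expected rise from baseline | Limit crossed |
|---|---|---|---|
| +9, day 1 | one 2 mL/kg bolus | about +10.3 to +10.5 | relowering (≥10); not primary (>12) |
| +17, day 2 | one 2 mL/kg bolus | about +18.3 to +18.5 | relowering (≥18) and primary (>18) |
| +9, day 1 | 6 h at 0.5 mL/kg/h | about +10.9 to +11.3 | relowering; not primary |
| +9, day 1 | 6 h at 1 mL/kg/h | about +12.8 to +13.6 | relowering and primary (>12) |

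The slow-arm rows assume a maintained rate. If the rate rule calls for an increase, the rise is larger.

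**3. The 130 mmol/L limit.** One bolus at s = 130 adds 0.002 × 383 / 0.502 = 1.53 or 0.002 × 383 / 0.602 = 1.27, giving about 131.3–131.5. That exceeds the goal. It reaches the ≥18 trigger only if the initial sodium was about 113 or lower (131.3 − 18 = 113.3; 131.5 − 18 = 113.5).

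**4. Sensitivity.**

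- Widening body water to 0.45–0.60 L/kg and current sodium to 114–134 gives 1.3–1.8 mmol/L per bolus. From +9 the trigger is still met throughout.
- From +8, the same range gives about +9.3 to +9.8, below the trigger.
- The fixed 100 mL for unknown weight, with 42 L of body water, adds about 0.9, so +9 becomes about +9.9, also below it.

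For a bolus, the problem therefore sits at the top of the goal range, not across it.

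**The case against.** **Saline does not stop only on the joint condition.** Relowering discontinues active treatment on sodium alone, whatever the symptoms. This stands, and the point is limited to the region below the trigger.

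**The goal is itself joint, so the stop rules follow it.** Goal, repeat rule and ceiling can be read as an ordered sequence, and the 1 mmol/L gap is a clinical choice. That is fair as far as it goes. But the goal also has an upper end, and the repeat-dose and rate rules carry a patient past it without saying that this is intended.

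**The setting is softer than a binding rule.** The doses are mostly recommended. The Discussion motivates repeat boluses by falling or unchanged sodium, not by a patient already at +9. Fig. 4 is not shown and may contain the missing branch. All of this lowers certainty. However, the Discussion still ends the repeat boluses on target level together with symptom relief.

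**Larger effects might be inferred from the Background.** It cites "prompt infusion of 100–150 mL of 3% saline over 10–20 min to increase the sNa by 4–6 mmol/L during the first hour". A reader might take this as 4 mmol/L per 100 mL and conclude that one bolus takes +9 to about +13, or that any rise of +6 or more will cross +10. The document does not support that. The figure is what the guideline infusion aims for, not a measured effect of one dose, and the Discussion describes that infusion as repeatable once or twice. Mixing gives about a third of it.

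**Bias between arms might be inferred.** The trial is open-label and symptom relief is a judgement, so a reader might conclude that knowledge of the arm shifts the primary event rate in one direction. The documents do not establish this. The joint rule is in both arms, and the goal and relowering strategy are stated to apply equally.

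**Conclusion.** The point holds in limited form. As written, both arms on both days direct more saline to a patient who is at the top of the sodium goal and still symptomatic. That is expected to exceed the plan's goal and, from +9 or +17, to meet its relowering trigger. At 130 mmol/L the goal is exceeded, but the trigger is met only with a low initial sodium.

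On day 1 one bolus from +9 leads to relowering, not to a primary event. Primary events are expected after one bolus from +17 on day 2, and after six more hours at a maintained 1 mL/kg/h from +9 on day 1.

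These sizes rest on the mixing assumptions above. Crossing is expected, not certain, because water losses or gains can move the next value either way. The document gives no basis for estimating how often the state arises, so no effect on the overall event rate, and none on the difference between arms, is claimed. It is still worth correcting, because it touches patient safety and the primary outcome directly.

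**What to change.** Reconcile the treatment goal, the four stop-rule sections (bolus and slow arms, days 1 and 2) and the relowering paragraph in Safety issues. Do the same for Fig. 4 if it carries the same wording. The text should state what applies when sodium is within or at the top of its goal range, including 130 mmol/L on day 2, and symptoms persist. The repeat-dose and rate rules should then no longer contradict the goal's upper limit and the relowering trigger. Use the same words in both arms. Which clinical rule to adopt is for the investigators.

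No added analysis is needed. In particular, splitting primary events by the reason saline was continued would condition on something that happens after randomisation.

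The cost is small: rewording of a few paragraphs and possibly one figure. The one downside is that recruitment began in August 2016, so patients already treated under the present wording must be identified.
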